#### Effect on healthcare equity

The effects of the intervention on the equitable provision of healthcare across the outcome measures will be assessed. The data points that will be used to assess the effects on equity include: average monthly household incomes (less than 200; 200–900; 901–1824; 1825–3054; and > 3055 Israeli new Sheqel), mother’s years of education (<10 years, 10–13 years, > 13 years), age at marriage (less than 20; 21–25 years; 26–30; 31–35; 36–40; greater than 40 years), and age at first pregnancy (less than 20; 20–25; 26–30; 31–35; 36–40; greater than 40 years).

### Timeline

The intervention sites have used the eRegistry exclusively for an average of 20 weeks (median of 16 weeks) prior to start of recruitment to ensure familiarity with the system while transitioning from paper files to the eRegistry (Fig. 5). The recruitment of new enrollments needed to reach the target sample size is expected to take approximately 8 months. There will be a follow-up period of another 8 months to capture adverse pregnancy outcomes for these new enrollments.

**Fig. 5 Fig5:**
[figure not shown]
SPIRIT figure. Schedule of enrolment, intervention, and assessments. *eRegistry* electronic registry

### Sample size

Sample size calculations for primary outcomes were performed in STATA (StataCorp. 2015, Stata Statistical Software: Release 14; College Station, TX, USA) “clustersampsi” using a 5% significance level and an assumed a priori intracluster correlation coefficient (ICC) of 0.01 for adverse pregnancy outcomes and 0.04 for the process outcomes [27]. Table 5 shows the estimated prevalence of primary outcomes for sample size calculations. We made sample size calculations to achieve a power of 90% based on an estimated average number of new pregnancies for 8 months in the study PHC. With 120 clusters recruiting for 8 months (with a minimum average cluster size of 44 in the year 2013), we will have more than 90% power to detect a relative 25–30% change in the composite adverse pregnancy outcome. With this sample size, we will have more than 90% power to detect a 15–25% change in the process primary outcomes. Effects of clustering and unequal cluster sizes have been accounted for in the sample size calculations (design effect = 1.75 for adverse pregnancy outcomes and 3.99 for process outcomes, and coefficient of variation of cluster size = 0.85) [28].

**Table 5 Tab5:** Assumed prevalence for primary outcomes for calculations of sample size

Outcome measure	Control group prevalence
Adverse pregnancy outcomes: composite of any of the five conditions below, accounting for coexistence of conditions in 10% of women	0.145
1. Moderate or severe anemia at admission for labor	0.0225
2. Large-for-gestational age baby at delivery	0.054
3. Small-for-gestational age baby at delivery undetected during pregnancy	0.057
4. Malpresentation at delivery undetected during pregnancy	0.02
5. Severe hypertension at admission for labor	0.01
Process (adherence) outcomes	0.40–0.60

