### Statistical methods

Data will be analyzed using STATA version 14 or later (StataCorp. 2015. Stata Statistical Software: Release 14*.* College Station, TX, USA). Primary analyses will be according to intention-to-treat comparing control and intervention groups using individual-level data taking the design effect of the clustering into account. In addition, we will undertake a per-protocol analysis. A baseline table with summary measures for the following background characteristics of participants will be reported: maternal age, parity, average monthly household income, education, medical history, obstetrical history, body mass index, blood pressure at booking visit, hemoglobin at booking visit, urine stick results for glucose at booking visit, birth weight, and fetal presentation at term. We will first undertake a cluster-level analysis for the primary and secondary outcomes. We will then perform analyses on individual-level data. All primary outcomes of the study will be measured as proportions. Comparisons of categorical variables will use generalized estimating equations (GEE) with a log link. We will use two-sided statistical tests and 95% confidence intervals for descriptive statistics and effectiveness estimates. In order to take into account the inherent clustering in our trial design, we will use random effects models. The effect of the intervention on the risk and prevalence of outcomes will be reported as relative (risk ratios (RR) and prevalence ratios (PR)) and absolute (risk difference and prevalence difference) measures of effect. Effectiveness will be calculated as 100 × (1 – RR) and 100 × (1 – PR) as appropriate. We will consider adjusting for confounders if there are baseline imbalances in the trial arms for variables that are strongly associated with the primary outcomes. We will perform complete case analyses and consider appropriate imputations for missing data. We will employ spider graphs in order to graphically display the effect of the intervention and whether a disproportionately large part of the effect can be ascribed to extreme effects in a few large clusters. In the rare event of protocol violations such as withdrawal of the eRegistry from an intervention PHC, data from these clusters will be excluded for women enrolled from the time of violation and onwards. All data on the pregnant women who maintain allocation, irrespective of from which cluster they receive care, will be included in the analyses. For those women that switch from intervention to control PHC, they will be analyzed as randomized in the primary, intention-to-treat analyses. In the per-protocol analysis, only data prior to switching clinics will be used and the rest will be treated as missing data. We will undertake instrumental variable analyses to better estimate the field efficacy of the intervention, in anticipation of possible nonadherence to the intervention [30]. For this analysis, the random allocation to the two arms of the CRCT will be the instrument. To enable this analysis, we will capture backdated data entry into the eRegistry from paper back-up (provided for use in cases of power outages and internet disruptions) to assess actual receipt of the intervention by the pregnant women. We will present additional analyses of quality of antenatal care measures in order to gain better understanding of the primary process (adherence) outcomes of the trial. These include: the proportion of women booked for care that both utilize and receive appropriate care; the probability of a woman affected by pregnancy complications to be successfully identified and managed; and provider-centric performance (the proportion of visits in which timely and appropriate care is provided).

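### The stated power of more than 90% for the composite adverse pregnancy outcome does not hold at the 25% end of the range: the protocol's own inputs give about 85% there and reach 90% at about a 27% relative reduction

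*Protocol article*

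**What the plan says.** All design inputs except allocation and sidedness stand in the Sample size section and its Table 5.

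- Composite claim: "we will have more than 90% power to detect a relative 25–30% change in the composite adverse pregnancy outcome".
- Process claim: "we will have more than 90% power to detect a 15–25% change in the process primary outcomes".
- Correlation and alpha: "using a 5% significance level and an assumed a priori intracluster correlation coefficient (ICC) of 0.01 for adverse pregnancy outcomes", with an ICC of 0.04 for the process outcomes.
- Size: 120 clusters recruiting for 8 months, with 44 given as a minimum average cluster size.
- Clustering: design effects of 1.75 (adverse outcomes) and 3.99 (process outcomes), with a coefficient of variation of cluster size of 0.85. The section says that unequal sizes are already allowed for.
- Control prevalence (Table 5): a single value of 0.145 for the composite, described as "accounting for coexistence of conditions in 10% of women", and a range of 0.40–0.60 for the process outcomes.

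The Allocation section gives 1:1 randomization. The Sample size section does not state sidedness, but Statistical methods does: "We will use two-sided statistical tests and 95% confidence intervals".

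**The concern.** A range of detectable effects needs something that varies to produce it. The process outcomes have that, because their control prevalence runs from 0.40 to 0.60. The composite does not: it has one prevalence, one ICC, one cluster size and one design effect. For a reduction there is therefore one effect at which power equals 90%, and a claim of more than 90% across a range must hold at its smallest member, 25%.

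The composite is the trial's primary health outcome, and the section sets 90% as the target. If power at 25% is really about 85%, the type II error at the smallest effect the sentence covers is about 15% rather than under 10%. A reader who takes the sentence at face value would credit the trial with more sensitivity to a 25% reduction than it has.

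**Working it through.** **Inputs.** K = 60 clusters per arm (120 at 1:1), mean size m = 44, ICC = 0.01, CV = 0.85, control prevalence p1 = 0.145, two-sided alpha 0.05 (z = 1.96). No loss is assumed.

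**Step 1: reproduce the stated design effects.** DE = 1 + [(CV² + 1)m − 1] × ICC, where CV² + 1 = 1.7225 and 1.7225 × 44 = 75.79.

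- Adverse outcomes: 1 + 74.79 × 0.01 = 1.748 (stated 1.75).
- Process outcomes: 1 + 74.79 × 0.04 = 3.992 (stated 3.99).

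Both match, so this is the formula and these are the inputs that the protocol used.

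**Step 2: effective sample size.** 60 × 44 = 2640 women per arm, and 2640 / 1.75 = 1508.6 effective women per arm.

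**Step 3: power at a 25% relative reduction.** p2 = 0.145 × 0.75 = 0.10875 and the difference d = 0.03625.

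- Null standard error, with pooled p = 0.126875: √(2 × 0.126875 × 0.873125 / 1508.6) = 0.01212.
- Alternative standard error: √[(0.145 × 0.855 + 0.10875 × 0.89125) / 1508.6] = 0.01210.
- z for power = (0.03625 − 1.96 × 0.01212) / 0.01210 = 1.033, so power is 84.9%.

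**Step 4: the rest of the stated range.**

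| Relative reduction | Intervention prevalence | Power |
|---|---|---|
| 25% | 0.1088 | 84.9% |
| 26% | 0.1073 | 87.7% |
| 27% | 0.1059 | 90.1% |
| 28% | 0.1044 | 92.2% |
| 30% | 0.1015 | 95.3% |

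Power reaches 90% at a 26.9% relative reduction. At 25%, 90% power would need about 1770 effective women per arm. At a design effect of 1.75 that is 1770 × 1.75 ≈ 3098 women, or about 71 clusters of 44 per arm (3098 / 44 = 70.4) against the planned 60.

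**Step 5: does another choice of method or input rescue 25%?**

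| Variant | Power at a 25% reduction |
|---|---|
| Unpooled variance | 85.0% |
| t reference, 118 df | 84.4% |
| Arcsine | 85.1% |
| Log risk ratio | 84.5% |
| m = 44.8 (8061 / 120 × 8/12), DE 1.75 | 85.5% |
| m = 40.4 (8061 / 133 × 8/12), DE 1.75 | 81.8% |
| Composite prevalence 0.147 (component sum 0.1635 less 10%) | 85.5% |
| Composite prevalence 0.1635 (component sum, no overlap) | 89.4% |
| One-sided 5% test | 91.1% |
| No CV inflation, DE = 1 + 43 × 0.01 = 1.43 | 91.2% |

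Only the last two pass 90%. The one-sided test conflicts with the two-sided testing in Statistical methods, and DE 1.43 conflicts with the stated 1.75. Either could be where the figure came from, but the document confirms neither.

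**Step 6: the process sentence, for comparison.** Effective n = 2640 / 3.99 = 661.7 per arm. Read as percentage points, a 15-point rise has over 99% power from 0.40, 0.50 or 0.60. Read as relative, 90% power is reached at increases of about 22%, 18% and 14% from 0.40, 0.50 and 0.60.

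**The case against.** The best defence is that 25–30% is a loose band around the detectable change and not a claim about each value in it. The 90%-power reduction of 26.9% does lie inside the band, and on that reading the sentence is imprecise and not grossly wrong. It still does not rescue the lower end: the words are more than 90% power, and with one assumed prevalence no scenario exists in which 25% would be the detectable reduction.

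A second defence is that 44 is called a minimum average, so actual clusters may be larger. With the design effect recomputed, a mean of 53 gives about 88% power and a mean of 60 about 90%. But 60 is roughly the 12-month enrolment, and the calculation is for 8 months. The 2013 figure of 8061 women over 120 clusters gives only 44.8 in 8 months.

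It also stands that the gap is modest, that most of the stated range does exceed 90%, and that the planned confidence intervals will show what a null result excludes.

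Three stronger readings are tempting and should not be adopted.

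- **That the process sentence is wrong too.** A 15% relative increase from 0.40 has only 60% power, and from 0.50 only 78%. But that sentence does not say relative, and in percentage points the claim is amply met. If relative, the changes of 22%, 18% and 14% largely match the stated 15–25% across the prevalence range. Pairing the smallest change with the lowest prevalence is a combination the sentence does not assert.
- **That unlinked births lower power further.** The document gives no linkage rate. Data extraction methods describes merging births from public, private and NGO hospitals, with the mothers' unique identifiers as the key for the public-hospital data, and the Discussion expects minimal loss.
- **That increases in the composite should be judged as well.** The composite is adverse and the trial tests superiority, so a reduction is the direction that matters.

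**Conclusion.** The composite power statement is wrong as written at its lower end. On the protocol's own inputs, a 25% relative reduction has about 85% power, 90% is reached at about 27%, and 30% has about 95%. The overstatement is about 5 points of power at 25%, or about 2 percentage points in the smallest relative reduction detectable with 90% power.

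This rests on 60 clusters of 44 per arm, a design effect of 1.75, control prevalence 0.145, two-sided 5% testing and no loss. It does not depend on the choice of two-proportion formula, since the methods tried give 84.4% to 85.1%. The two-sided assumption comes from Statistical methods, because the Sample size section is silent on it.

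The correction concerns a reported figure for a primary outcome. It does not show that the trial is too small for the effects at the upper part of its stated range, nor does it touch the planned analysis. The process sentence calls for clarification only.

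**What to change.** Restate the composite sentence along these lines: *with 120 clusters averaging 44 women, power is about 90% for a 27% relative reduction in the composite (about 85% for 25% and about 95% for 30%), two-sided 5%.* If the original calculation used a one-sided test or left out the inflation for unequal cluster sizes, say so and correct it.

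As an optional clarification, state whether the 15–25% for process outcomes is relative or in percentage points. If it is relative, tie each end to a control prevalence: 90% power needs an increase of about 22% from 0.40, 18% from 0.50 and 14% from 0.60.

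The cost is the rewording of one sentence, or two with the clarification, and a slightly less favourable figure. Enrolment, design and analysis stay as they are.

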### Recruitment

The national implementation of the eRegistry is currently underway in Palestine. A total of 327 care providers from the intervention clinics were trained in the use of the eRegistry in batches of up to 20 participants per day of training. All care providers in the intervention PHC have had a day of introduction and 2 days of training in the use of the eRegistry. Each training session consisted of hands-on clinical case simulations focusing on data entry and documentation, clinical decision support functionalities, retrieving records, reporting routines, and general software maintenance. Initial group training sessions were followed up with visits to the PHC by the national implementation team to provide technical support to care providers [26]. No financial or nonfinancial incentives are provided to public health officers or care providers at the PHC.

### Allocation

PHC were randomized to either the control or the intervention group with a 1:1 allocation. We adopted an approach of stratified and covariate constrained randomizations. We stratified by district and constrained on: number of new enrollments of pregnancies per year (which reflects size and thus PHC level and days of operation per week); laboratory availability (which may affect care provider performance of screening tests); proportion of new enrollments above 40 years of age (which reflects general health and risk status); and proportion of primiparous women (which reflects risk status). A set of 10,000 randomization allocations were first generated. The 10% best and balanced allocations, with least differences between the two arms for the given covariates, were then identified. Finally, we randomly selected one of these allocations for the trial [29]. Statisticians at the Center for Intervention Science in Maternal and Child Health (CISMAC), University of Bergen, Norway, performed the randomization independently without any influence from the principal investigator or study staff. The list of participating clinics can be found in Additional file 3.

### Blinding

Participating PHC staff cannot be blinded to the allocation due to the nature of the intervention. During data collection for process outcomes, data collectors cannot be blinded to the allocation due to the nature of the intervention (paper collection versus electronic). The data collectors are, however, independent of the study team. They have received standardized training to collect a large number of routine indicators and data points for the eRegistry while being blinded for the outcome measures of this trial. The adverse pregnancy outcomes are collected independently by hospital staff using their routine health information system which is not linked to the eRegistry, effectively blinding hospital data collection to the allocation. Data analysts will be blinded to the allocation for all data management and computation of raw data for outcome measures, and for all analyses of primary and secondary outcomes. At the end of follow-up, each primary outcome will be analyzed separately. Dummy randomization variable codes will be generated for initial analyses of all primary outcomes by CISMAC (e.g., A and B, C and D, E and F, G and H, I and J), and the code will be provided as allocation groups (intervention versus control for each set) by CISMAC only after the completion of analyses.

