Timely and appropriate screening and management of abnormal fetal growth	Case records data from the PHC in the eRegistry	Registrations continuously at point of care, data export to the trial monthly	Proportion of women attending ANC who receive: 1. first fundal height measurement at 16–20 weeks, and 2. fetal growth monitoring at every ANC visit, and 3. referred to ultrasound if discrepancy between fundal height and gestational age, and 4. referred to high-risk clinic if ultrasound confirmed fetal growth restriction.
Timely and appropriate screening and management of diabetes in pregnancy	Case records data from the PHC in the eRegistry	Registrations continuously at point of care, data export to the trial monthly	Proportion of women attending ANC who receive: 1. diabetes screening at booking, and 2. screening with random blood sugar test at 24–28 weeks, and 3. referred to high-risk clinic if random blood sugar test or glucose challenge test ≥ 140 mg/dl.

*ANC* antenatal care, *eRegistry* electronic registry, *PHC* primary healthcare clinics

**Table 3 Tab3:** Primary adverse pregnancy outcomes, source of data, measurement sequence, and definitions

Adverse pregnancy outcomes	Source of data	Measurement sequence	Definitions
Moderate or severe anemia at admission for labor	Hemoglobin admission data from hospitals in the eRegistry (public, private, and NGO hospitals)	Registrations continuously at point of care, data export to the trial monthly	Moderate anemia: hemoglobin greater than 7 and less than 9 g/dl; severe anemia: hemoglobin < 7 g/dl
Severe hypertension at admission for labor	Blood pressure admission data from hospitals (public, private, and NGO hospitals) in the eRegistry	Registrations continuously at point of care, data export to the trial monthly	Severe hypertension: systolic blood pressure ≥ 160 mmHg and/ or diastolic blood pressure ≥ 110 mmHg
Malpresentation at delivery undetected during pregnancy	Presentation at delivery data from hospitals (public, private, and NGO hospitals) in MCH registry	Registrations continuously at point of care, data export to the trial monthly	All non-cephalic presentations at or after 36 weeks of gestation and at labor
Small-for-gestational age baby at delivery undetected during pregnancy	Birth weight data from hospitals (public, private, and NGO hospitals) in the eRegistry	Registrations continuously at point of care, data export to the trial monthly	Small for gestational age: less than 2549 g [34]

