### Data extraction methods

Care providers using the eRegistry or the paper records will continuously enter data during patient care. All data from completed paper records (after delivery of the baby) from the control PHC are routinely computerized by trained registry staff into the eRegistry every month. Double data extraction is carried out on approximately 10% of all the paper-based files for quality assurance purposes. Birth outcome data from public hospital maternity wards and delivery units are collected independently by hospital staff using their routine health information system which is not automatically linked to the eRegistry. These data are routinely exported from the hospital health information system’s national server every month, and merged into the eRegistry using the unique identifiers of the mothers. Data on births from all other hospitals with maternity wards and delivery units, including private hospitals and those run by NGOs, are collected by the Palestinian MoH staff using a standardized form on a monthly basis, and also merged into the eRegistry. For this CRCT we will only use anonymous data extracted from the eRegistry in accordance with the SOP of the Palestinian maternal and child health eRegistry for routine registry operations and use of data for research purposes [26].

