## Discussion

Electronic health information systems and programs are frequently tested in isolation, often as pilots or with less robust study designs [31]. This CRCT aims to contribute to filling this evidence gap. In order to study effectiveness of the intervention in the health system, we have designed a pragmatic CRCT. We have worked closely with the Palestinian MoH to plan the intervention and the timelines for the implementation of the eRegistry. All our communication strategies to the study clinics have always been through the Palestinian MoH via established channels within the health system in an attempt to keep monitoring of sites robust but as close to real-world settings as possible. We have striven to maintain generalizability of study findings by including a large representative sample of PHC and having no individual-level eligibility criteria. Data for outcome measures are derived from existing data collection pathways for the eRegistry in Palestine. The design and implementation of this CRCT places emphasis on the outcomes, as well as the feasibility of their measurement, in registry settings within the health system. Loss to follow-up is expected to be minimal since all our data sources are part of the eRegistry. We have designed outcome measures to directly reflect the effect of the intervention within the setting of an electronic registry, justifying the use of secondary data, where the process outcomes are based on the care providers’ own documentation of process, and health outcome measures are based on data collected independently from the care provider.

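### Blinded, independent collection of the adverse outcomes is supported only for public-hospital extracts, and it does not extend to the antenatal-detection qualifier in two of the five components

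*Protocol article*

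**What the plan says.** The Blinding section of the protocol article states, with no exception by type of hospital: "The adverse pregnancy outcomes are collected independently by hospital staff using their routine health information system which is not linked to the eRegistry". It takes this as "effectively blinding hospital data collection to the allocation".

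The Data extraction methods section uses a similar sentence but limits it: "Birth outcome data from public hospital maternity wards and delivery units are collected independently by hospital staff using their routine health information system". It describes a second route for every other hospital that has deliveries, private and NGO ones among them. Their records "are collected by the Palestinian MoH staff using a standardized form on a monthly basis, and also merged into the eRegistry". It also says only that the public-hospital system has no automatic link to the eRegistry; the data are merged in each month by the mother's identifier.

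Table 3 draws the adverse outcomes from public, private and NGO hospitals. Two of its five components carry a condition on antenatal detection: malpresentation, and "Small-for-gestational age baby at delivery undetected during pregnancy". For both, the listed source is hospital data only (presentation at delivery, birth weight).

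The Discussion generalises that "health outcome measures are based on data collected independently from the care provider".

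**The concern.** The clinics are open-label, so blinded and independent outcome data are the main protection the article claims for the health outcome. Two statements carry that claim, and each is wider than the rest of the article supports.

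First, the reason given for blinding (hospital staff, separate system) does not describe how births outside public hospitals are collected.

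Second, birth weight or presentation at delivery cannot show whether the condition had been picked up before labour. That information sits in the antenatal record, and the intervention acts directly on how that record is kept. If the eRegistry leads providers to document detection more completely, cases leave the undetected category and the composite falls, even if no mother's or baby's condition has changed.

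**Working it through.** **Who collects.** Set side by side:

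| | Blinding section | Data extraction section |
|---|---|---|
| Public hospitals | hospital staff, unlinked system | hospital staff, no automatic link, merged monthly |
| All other hospitals | same (no exception made) | ministry staff, standardized form, merged monthly |

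Table 3 counts births from both rows, so the Blinding statement is supported for the first row only. The share of births in the second row is not given and cannot be computed.

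**Where detection is recorded.** Tables 2 and 4 place antenatal screening and referral for fetal growth and malpresentation in the clinic case records. The Blinding section says that clinic staff and the collectors of process data are not blinded. Records are electronic in intervention clinics and paper in control clinics. The Discussion adds that high-risk clinics also use one medium or the other according to the referring arm, and that process data depend on how fully providers document.

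**How much of the composite carries the qualifier (Table 5).**
- Sum of components: 0.0225 + 0.054 + 0.057 + 0.02 + 0.01 = 0.1635.
- Conditional on detection: 0.057 + 0.02 = 0.077.
- Share of summed prevalence: 0.077 / 0.1635 = 47.1%.

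The stated composite is 0.145 after 10% coexistence (0.1635 × 0.9 = 0.147, close to it). Table 5 does not say which conditions coexist, so the share of composite cases that count only through one of these two components can only be bounded. The other three sum to 0.0865, so it is at least (0.145 − 0.0865) / 0.145 = 40% and at most 0.077 / 0.145 = 53%.

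**What documentation alone could do (illustration).** The reclassified fractions x are assumed; the article gives none. Spread the coexistence evenly: 0.077 × 0.145 / 0.1635 = 0.0683 of the 0.145. The intervention-arm composite is then 0.145 − 0.0683x with no change in health.

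For the chance of a significant result, the design effect is 1 + ((1 + 0.85²) × 44 − 1) × 0.01 = 1.748, which reproduces the stated 1.75. Effective n per arm is 60 × 44 / 1.748 = 1,510. The chance is Φ(difference / SE − 1.96), against 2.5% in that direction with no bias.

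| x (assumed) | Composite | Risk ratio | Chance of a significant benefit |
|---|---|---|---|
| 10% | 0.1382 | 0.953 | 8% |
| 20% | 0.1313 | 0.906 | 19% |
| 30% | 0.1245 | 0.859 | 38% |
| 50% | 0.1109 | 0.765 | 80% |

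With the 40% and 53% bounds in place of 47%, x = 20% lowers the composite by 8% to 11%.

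**The case against.** The strongest reply has four parts.

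*Ministry collectors.* A reader might infer that ministry staff are unblinded, because the ministry is rolling out the eRegistry and its supervisors visit clinics in both arms. The article does not support that. It does not say that those who abstract births know the allocation or the antenatal clinic, or that they are the supervisors. They cover births in all non-public hospitals on a standardized form, with merging described afterwards. This part of the reply stands: blinding there is unsupported, not shown to be absent.

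*The Blinding section claims less than it seems.* Its conclusion concerns hospital data collection, not the detection classification, and the rule for the qualifier may sit in a fuller document. That is fair. The detection point therefore contradicts the Discussion's independence statement, not the Blinding section, and it is an inference from the component names. But no hospital source listed in Table 3 could supply antenatal detection, and the only records described for it are those of the clinics.

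*Safeguards.* Analysts are blinded when outcomes are computed, paper and electronic files hold the same items, and about 10% of paper files are extracted twice. These limit errors in extraction and derivation. They do not touch a difference in what providers wrote down.

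*The size.* A reader might take 47% as the share of composite events that rest on unblinded data. It is a share of summed prevalences before coexistence. Moreover, the birth weight and presentation in these components are still hospital measurements; only the qualifier depends on the clinic.

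**Conclusion.** The concern holds in a limited form. The blinding statement is supported for public-hospital extracts only; for other hospitals the article leaves the matter open. The independence statement fails for the detection qualifier in two of the five components, which make up 0.077 of 0.1635 (47%) of summed prevalence. Anemia, severe hypertension and large-for-gestational-age do not depend on clinic detection.

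The possible bias is real, but its size is unknown. It rests on the assumption that the intervention arm documents detection more completely, and on how much. Reaching the 25–30% target through documentation alone would need about half or more of the undetected cases to be reclassified (0.25 / 0.471 = 53%). Smaller fractions would still add to an apparent benefit. Nor is every additional recorded detection an artefact, since better detection is part of what the intervention is meant to achieve. The current composite cannot separate the two.

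**What to change.** 1. In the Blinding section and the Discussion, confine the blinding and independence statements to the public-hospital extracts and the raw hospital measurements, and say that the detection qualifier comes from the antenatal record.
2. State the blinding status of the ministry staff who collect births from the other hospitals.
3. Keep the current composite as primary. Add a sensitivity analysis of the composite that counts all small-for-gestational-age and malpresentation at delivery, whatever was detected antenatally, so that it uses hospital data alone.

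The first two changes are wording; the third uses data already collected. The downside of the third is that it also counts detected cases, so it answers a slightly different question and may dilute a true effect on detection. It should be read alongside the primary result, not in place of it.

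An analysis restricted to public-hospital births is not a good substitute. Place of delivery is settled after randomization and may be affected by the referral prompts in the intervention, so such a subset should be left out or reported as descriptive only.
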